**Fig. 2 Fig2:**
[figure not shown]
Schematic representation of the Loughborough Soccer Passing Test (LSPT). Ali A et al. [21]

The second examiner will also be responsible for recording the penalty time points accrued during the test. Thus, the examiner will stay in a position that all four target areas can be viewed. Penalty times will be appointed for the following errors:5 s for missing the bench completely or passing the ball towards the wrong bench3 s for missing the target area3 s for handling the ball2 s for passing the ball outside of the designated area2 s if the ball touches any of the cones1 s for every second spent over the designated 43 s needed to complete the test1 s will be subtracted from the total time if the ball hits the 10-cm strip in the middle of the target

Two trials of LSPT will be performed in each of the soccer training assessments, and the best score taken as the performance score.

#### Loughborough Soccer Shooting Test (LSST)

The LSST is also a validated test [21] that allows us to evaluate the capacity of a player (in this case our subjects) to score a goal within a simulated soccer gameplay scenario. This particular aspect of the test reproduces real-life conditions of gameplay, thus yielding a more real score of the subject’s performance.

Immediately following completion of the LSPT protocol, the participants will be evaluated with another capillary finger glucose level. After that, the trainer will proceed with the evaluation of the LSST (see Fig. 3).

**Fig. 3 Fig3:**
[figure not shown]
Schematic representation of the Loughborough Soccer Shooting Test (LSST). Ali A et al. [21]

For this test, the boundary lines will be measured and marked on the floor using a 5-cm yellow tape. The “shooting zone” will be a square area (8.5 × 8.5 m), with the nearest line marked at a distance of 16.5 m from the goal line. Four tall traffic cones will be placed on each corner of the shooting zone. A standard gymnasium bench will be placed in the middle of the far side of the zone to act as a rebound board. The full-sized goal, measuring 2.44 × 7.32 m, will be split into various scoring zones marked with a 5-cm tape (Fig. 3); this whole area will be drawn on a piece of polyethylene sheeting measuring 7 × 9 m.

To enhance the reality of the test, a static, life-size mannequin goalkeeper will be used. The figure will measure 1.9 m tall and 1.22 m at its widest point at the base and the arm span. The goalkeeper will be positioned 5.5 m in front of the goal line, and the side (right or left) will be changed depending on the experimenter’s instructions. The goalkeeper will be set on a base with four wheels to allow for ease of movement across the goal center during experimentation.

When completing the LSST protocol, the ball will be initially be placed on the marked cross in the middle of the shooting zone (Fig. 2). The starting position for the participant will be facing away from the goal within 0.5 m distance of the ball. On the evaluator’s call, the player will sprint to the appropriate cone, will touch the top of it, and then will return to play a “rebound” pass against the bench; the participant will turn and control the ball if necessary, and then will shoot at the goal while within the shooting area.

The player then will follow up his shot by sprinting past the goalkeeper. Each trial will consist of 10 shots with 1-min resting periods between each shot sequence. There will be six trial orders that will be randomly selected for each player. The goalkeeper mannequin will be positioned to the opposite side of the “left/right” call.

To prevent players from attempting shots at an “unrealistically slow” speed, a minimum value of 64 km · h^-1^ will be set for the shot to be valid for this test protocol. The Gamma SpeedTrac X radar gun (Gamma Sports, Pittsburgh, USA) equipment will be used to measure the shot speed.

During match play, the optimal placement of a ball to beat the opposing goalkeeper is at the top and bottom corners of the goal and the points associated with each scoring zone will reflect this (Fig. 2). Furthermore, a coach would normally encourage the players to shoot across the goalkeeper towards the open space of the goal [12]. To replicate this within the LSST, the players will be told that they can only score points if the ball strikes the open side of the goal, i.e., the half not covered by the mannequin goalkeeper.

Both left and right feet will be used during the LSST. The trial orders will be devised so that players have five shots for each foot per trial. The final score will be the mean of the total cumulative points accrued from all the shots on target. Those shots that were attempted from outside the shooting zone, took more than 8.5 seconds to complete, and/or were struck at less than 64 km · h^-1^, will be completely disregarded.

The assessments will have the same order for every participant regardless of the interventional arm allocation and will be conducted as follows: (1) LSPT numbers 1; (2) LSST numbers 1; (3) LIST-P; (4) LSPT numbers 2; and (5) LSST number 2 (Fig. 4).

**Fig. 4 Fig4:**

Schematic representation of the order of soccer assessments according to the protocol. *LIST-P* Loughborough Intermittent Shuttle Test Prescribed and Self-Paced, *LSST* Loughborough Soccer Shooting Test, *LSPT* Loughborough Soccer Passing Test

Additionally, as exploratory outcomes we will also assess cognitive functions, given that hypoglycemia has long been thought to influence these functions in people with diabetes mellitus. A field study of school-aged children with T1D has shown that low blood glucose level impairs patients’ sports performance and produces detrimental cognitive effects, as measured by math test performance [8]. In this sense we set forth to evaluate, as a secondary outcome, the effect of the 4-step method on the cognitive performance of the subjects, related also to the frequency of hypoglycemic events and to the performance in soccer indexed by the tests described. We hypothesize that besides showing an adequate safety profile (same or reduced number of hypoglycemic events), the 4-step method will also allow the subjects to achieve a better performance both in soccer and in cognitive testing (see Fig. 5 for a summary of the planned study interventions and assessments).

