**Methods/design:**

We designed a study protocol for a randomized, crossover, double-blinded, controlled trial, for the evaluation of the effect that a strategy of dietary and therapeutic modifications may have on safety and performance of persons with T1D in soccer training sessions and cognitive testing. Inclusion criteria comprise: age older than 18 years, more than 2 years since T1D diagnosis, low C-peptide level, a stable insulin regimen, HbA1c less than 9.0% and regular participation in soccer activities. Our primary outcome evaluates safety regarding hypoglycemia events in patients using dietary and therapeutic adjustments, compared with the performance under the implementation of current American Diabetes Association (ADA) usual recommendations for nutritional and pharmacological adjustments for exercise. Additionally, we will evaluate as secondary outcomes: soccer performance, indexed by performance in well-established soccer skill tests, cognitive functions (indexed by Stroop, digital vigilance test (DVT), Corsi block-tapping task (CBP), and rapid visual information processing (RVIP) tests), and glycemic control measured with a continuous glucose monitor (CGM).

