## Methods

### Research aim

The aim of this research is to assess the safety (evaluated as rate of hypoglycemia) that this 4-step strategy has on patients with T1D after completing a series of simulated soccer tests. As exploratory analysis, we will compare the performance of the skills required to achieve a good score in the selected test. We will also aim to identify an optimal pre-exercise blood glucose level associated with a better performance in simulated soccer tests. Finally, we will evaluate the effect of this 4-step strategy for blood glucose level control in the cognitive performance (indexed by neuropsychological evaluations testing executive functions, attention, working memory, psychomotor speed, and visual-spatial short-term memory) in patients diagnosed with T1D.

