### Primary outcome

We will compare the percentage of participants with one or more confirmed hypoglycemic episodes (≤60 mg · dL^-1^) in the next 24 h following the assessment session. Other safety-related end points include changes in the mean and variability of 24-h plasma glucose based on CGM. Percentages of participants with hypoglycemic events will be calculated as categorized by the ADA^70^ and will be analyzed during the day (daytime; 6:00 a.m. to 11:59 p.m.), during the night (nocturnal; 12:00 midnight to 05:59 a.m.), and any time of day or night (24 h).

Precisely, hypoglycemic categories will include the following: (1) any hypoglycemia (events whether confirmed by self-measurement or not and whether symptomatic or asymptomatic); (2) documented symptomatic hypoglycemia (symptomatic events with plasma glucose ≤60 mg · dL^-1^); (3) asymptomatic hypoglycemia (events confirmed by plasma glucose ≤60 mg · dL^-1^ but without symptoms); and (4) severe hypoglycemia (events requiring assistance by another person to administer carbohydrate, glucagon, or other therapy). Confirmed or severe hypoglycemia will include documented symptomatic or asymptomatic events together with severe events.

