### Statistical methods

In order to evaluate glucose control, we will also compare the two groups, using either Student’s paired *t* test or the Wilcoxon-Mann-Whitney test, in terms of CGM parameters that include: 24-h mean glucose levels, SD of 24-h glucose levels, area under the curve for 24-h glucose, mean amplitude of glycemic excursions, number of episodes of hypoglycemia (<60 mg · dL^-1^), time in hypoglycemia (<60 mg · dL^-1^) during a 24-h period, time in hyperglycemia (>180 mg · dL^-1^) during a 24-h period, and range of postprandial glucose increase. The range of glucose increase (from pre-meal to post-prandial peak levels) after breakfast, lunch, and dinner, will also be compared between the interventional groups, using either repeated measures analysis of variance (ANOVA) or the Kruskal-Wallis test, depending on the normality of the data distribution.

We will assess for data from the LIST-P, LSPT, and LSST, and the Stroop, DVT, DBT, and RVIP test scores obtained for each assessment session, for normality of distribution using histogram analysis, the Shapiro-Wilk test and the Kolmogorov-Smirnov test. We will use a logarithmic transformation for the correction of non-normal data and will subsequently test for the differences between groups using Student’s paired *t* test. In order to assess if the order of the intervention modified the performance of individual participants, we will calculate the difference of the scores obtained between the two types of interventions (real intervention minus sham 4-step method) and then we will define an intervention indicator variable that will take the value of 1 if the subject started with the real 4-step method, and 0 if the subject started with the sham 4-step method. We will then fit a linear regression model with the difference calculated as the response variable and the intervention indicator along with other relevant covariates (age, gender, BMI) as the independent variables. Moreover we will test for time effect over the performance of the participants in a time-varying regression model. Additionally, Pearson correlation coefficients will be calculated between each of the scores and the pre-exercise blood glucose level, searching for linear correlation between blood glucose values and the LIST-P, LSPT, LSST, and Stroop test scores.

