### Adverse event monitoring

An un-blinded group of physicians and physical trainers will be in charge of monitoring glucose derangements and physical injuries that may arise during the assessments. We have prepared protocol-based treatment and dietary interventions that follow guidelines established for both the usual recommendations and the 4-step method groups, which will be executed in the case of hyperglycemic or hypoglycemic events. Also, we will record any adverse events observed during the execution of the trial and, if required, report them directly to our Ethics Committee for further evaluation. Additionally, our technical team will check and calibrate each of the glucometers and CGM devices before using them in any of the protocol assessments.

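### The safety conclusion is worded on hypoglycemia only, and the planned comparison of time above 180 mg/dL is not tied to it, although the real 4-step arm receives less insulin overall

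*Protocol article*

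**What the plan says.** Three places in the protocol article word safety in terms of hypoglycemia:

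- Research aim: the trial is to "assess the safety (evaluated as rate of hypoglycemia) that this 4-step strategy has on patients with T1D".
- Primary outcome: the comparison is of the "percentage of participants with one or more confirmed hypoglycemic episodes" in the 24 h after the session. All four event categories, and the daytime, nocturnal and 24-h windows, concern hypoglycemia.
- The paragraph on cognitive outcomes after Fig. 4: the authors hypothesize that "besides showing an adequate safety profile (same or reduced number of hypoglycemic events), the 4-step method will also allow the subjects" to do better in soccer and cognitive tests.

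High glucose is covered elsewhere:

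- Primary outcome adds: "Other safety-related end points include changes in the mean and variability of 24-h plasma glucose based on CGM". No threshold or direction of harm is given.
- Statistical methods opens its list of CGM parameters with "In order to evaluate glucose control, we will also compare the two groups". The list includes "time in hyperglycemia (>180 mg · dL^-1^) during a 24-h period", along with 24-h mean, SD, area under the curve and time below 60 mg/dL.
- Adverse event monitoring says that treatment and dietary plans are ready, "which will be executed in the case of hyperglycemic or hypoglycemic events".

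**The concern.** A safety criterion that counts only low glucose suits a comparison in which the risk runs one way. Here the two arms take the same carbohydrate amounts, and the real arm takes less insulin after exercise: half the bolus at the post-exercise meal and 20% less basal insulin. Table 1 excludes anyone with detectable C-peptide, so participants' own insulin cannot be expected to make up the difference. The opposite risk, more time at high glucose, is therefore a plausible price of fewer lows.

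The article treats that risk as real. Its Background credits the method with protection against both low and high glucose, in trials of continuous exercise. Whether both protections carry over to soccer is open, and the wording of the safety verdict asks about only one of them. As written, an adequate safety profile could be claimed on equal or fewer hypoglycemic events while time above 180 mg/dL increased.

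**Working it through.** **1. Plan's own figure, for the number of completers.** Sample size gives 24, and 28 after 15% dropout. The base rate is not stated. Assuming 70% versus 30% (a 40-point difference), two-sided alpha 0.05 and 80% power:

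n = [1.96·√(2·0.5·0.5) + 0.842·√(0.7·0.3 + 0.3·0.7)]² / 0.4² ≈ 23.3, so 24. Then 24 × 1.15 = 27.6, so 28.

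The figure is reproduced. The point does not depend on it; it only sets the range of 24 to 28 completers used in step 5.

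**2. Insulin contrast, as a share of the usual dose** (Intervention, Control intervention, Table 2):

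| Dose | Real | Control, text | Control, Table 2 |
|---|---|---|---|
| Pre-exercise bolus | 0.50 | 0.75 | 0.25 |
| Post-exercise bolus | 0.50 | 1.00 | 1.00 |
| Snack bolus | none | none | none |
| Basal | 0.80 | 1.00 | 1.00 |

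Real minus control is −0.50 at the post-exercise meal and −0.20 for basal insulin. Before exercise it is −0.25 by the text but +0.25 by Table 2, because the text gives control 75% of the usual dose and the table a 75% reduction.

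**3. Does the real arm get less overall under both readings?** Assumption for illustration: basal share s of the daily total and four equal boluses b = (1 − s)/4 (breakfast, lunch, pre-exercise, post-exercise).

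- Real: 2b + 0.5b + 0.5b + 0.8s = 3b + 0.8s
- Control, text: 2b + 0.75b + b + s = 3.75b + s
- Control, Table 2: 2b + 0.25b + b + s = 3.25b + s

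| s | b | Real | Control, text | Control, Table 2 |
|---|---|---|---|---|
| 0.4 | 0.150 | 0.770 | 0.963 | 0.888 |
| 0.5 | 0.125 | 0.775 | 0.969 | 0.906 |
| 0.6 | 0.100 | 0.780 | 0.975 | 0.925 |

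Yes. The real arm gets less under either reading.

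**4. Carbohydrate not covered by bolus from 5:00 p.m.**, assuming usual doses match carbohydrate. Intake is 1.0 + 1.0 + 0.4 = 2.4 g/kg in both arms.

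- Real: 0.5 + 0.5 + 0.4 = 1.4 g/kg (58%)
- Control, text: 0.25 + 0 + 0.4 = 0.65 g/kg (27%)
- Control, Table 2: 0.75 + 0 + 0.4 = 1.15 g/kg (48%)

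The snack cancels. The between-arm difference is 0.75 g/kg (text) or 0.25 g/kg (Table 2); at 70 kg, 52.5 g or 17.5 g. From the post-exercise meal onward the two readings agree: real 0.5 + 0.4 = 0.9 of 1.4 g/kg (64%), control 0.4 of 1.4 g/kg (29%). All this is before the basal reduction.

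**5. What the trial could say about time above 180 mg/dL.** Paired 95% CI half-width, in SDs of the within-person difference, is t(0.975, n−1)/√n:

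- n = 24: 2.069/√24 = 0.42
- n = 28: 2.052/√28 = 0.39

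A two-sided paired t test at 0.05 has 80% power for differences of about 0.60 SD (n = 24) or 0.55 SD (n = 28). The article gives no SD and no hyperglycemia margin, so these cannot be turned into minutes or a pass/fail limit.

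**The case against.** The strongest reply is that hyperglycemia is already in the plan, and much of that reply stands. Four stronger readings are tempting, and the document does not support them.

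- *Safety is assessed on hypoglycemia and nothing else.* CGM mean and variability are named as safety-related, time above 180 mg/dL is a planned comparison, and hyperglycemic events are monitored. The end of the Background also hypothesizes fewer glycemic derangements and better control.
- *The trial could not tell better control from an upward shift of the whole glucose distribution.* It could. Mean, area under the curve, time below 60 and time above 180 mg/dL together would show such a shift.
- *Treated hyperglycemic events would not count.* Adverse event monitoring records any adverse event, and Statistical methods compares other adverse effects with the Fisher exact test. The wording is loose but excludes nothing.
- *Fewer lows follow by construction.* Under Table 2 the real arm takes more insulin than control before exercise. The real arm also switches the post-exercise meal and snack to low-GI food, which the Discussion credits with preventing a rapid glucose rise. The uncovered carbohydrate in step 4 ignores exercise and GI, so it shows the direction of the risk and is no forecast of hyperglycemia.

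It is also fair that the sentence after Fig. 4 is a parenthesis within a hypothesis, with no formal decision rule attached. However, it matches the Research aim, and nowhere does the article make the safety conclusion depend on a hyperglycemia result. A rise in mean glucose has no stated direction of harm either: it could come from fewer lows or from more highs.

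**Conclusion.** The point holds as a matter of what the safety claim rests on. The criterion is one-sided, the real arm receives less insulin overall for equal carbohydrate amounts, and time above 180 mg/dL sits outside the safety conclusion. The method could be described as having an adequate safety profile while that time rises, even though the rise would be measured and reported.

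The insulin contrast is about 77–78% of usual daily insulin against 96–98% (text) or 89–93% (Table 2). It rests on the assumed equal boluses and a basal share of 40–60%. The direction is the same under both readings; the size depends on which one applies. Nothing in the document shows that hyperglycemia will in fact worsen. This is a cheap improvement to the plan; the design and the primary comparison stay as they are.

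**What to change.** - Under Primary outcome, name CGM time above 180 mg/dL as a key safety endpoint in the same daytime, nocturnal and 24-h windows as hypoglycemia. Report it as a within-person difference with its 95% confidence interval.
- Reword Research aim and the paragraph after Fig. 4 so that any claim of adequate safety rests on hypoglycemia and this result together.
- State that a non-significant difference will not be read as proof of no worsening, since the interval will extend about 0.4 SD of the within-person difference to either side.
- Report treated hyperglycemic events descriptively only. Un-blinded physicians treat them under guidance set out for each arm, so a formal comparison would be open to bias.
- Separately, reconcile the control arm's pre-exercise insulin dose between the Control intervention text and Table 2, because the conflict reverses the pre-exercise contrast.

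The cost is protocol wording and one extra tabulation; the threshold and the CGM data are already in the plan. The downside is a safety claim that is harder to make.

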**Fig. 5 Fig5:**
[figure not shown]
SPIRIT flow diagram. (A summary of the planned study interventions and assessments)

Stroop testThe Stroop test is a commonly used neuropsychological tool that measures selective attention and mental processing speed among the cognitive functions that could be affected by attentional fatigue [22]. Campbell et al. utilized the Stroop test in a clinical trial that evaluated participants with T1D during physical activity in a sports camp. The investigators found that reading and color recognition ability were susceptible to impairment as a result of hypoglycemia [12].Commercially available Stroop Color and Word Tests (WPS Publish, Alaska, USA) will be used to assess cognitive processing in our participants. Scores will be determined for reading ability, color recognition, and interference; the latter will be used as an index of the subject’s capacity to maintain attention during the interference caused by the color changes in the typed words [23].Stroop testing will take place immediately following each soccer training session and during the morning evaluation at 8:00 a.m. on the next day. Each of these tests will take 2 to 5 min (time limit of 45 s per slide) for the participants to complete. Participants will be asked to complete the test using three slides: (1) read as many colored words as possible in 45 s; (2) name as many colors of a group of “X” letters as possible in 45 seconds; and (3) name the color in which a word is printed (e.g., “blue”, “green”, or “red” ink) and not the word itself, which is a name of a color (e.g., the word “red” printed in blue ink instead of red ink). Naming the color of the word during this “interference” takes longer and is more prone to errors than when the color of the ink matches the word that names the color [16]. Reading, color naming, and interference scores will be converted to *T* scores according to the manual of Golden and Stroop for further analyses.Digit vigilance testThe digit vigilance test (DVT) works as a measure of sustained attention and psychomotor speed. Participants will be asked to cross out a specific target number (6) as quickly as possible, which appears randomly within 59 rows of 35 single digits on two pages. The examiner will observe the subject's performance on the demonstration rows and then on the first five rows of the test to determine whether corrective feedback is required to discourage an inefficient or poorly motivated response style (e.g., going too fast and missing numbers or going too slow and focusing attention on each individual number). Total time and errors of omission will be recorded. For the first (practice) administration, all participants will be asked to complete the standard format (target = 6) [24].Corsi block-tapping taskThe Corsi block-tapping task (CBT) is widely used for the assessment of visual-spatial short-term memory, both in clinical practice and in experimental research settings. Basically, it is a span task and, as such, a visual-spatial analog to the digit span, as an index of verbal short-term memory. The examiner taps a sequence of blocks, which the participant must repeat subsequently in the correct sequential order. By increasing the length of the sequences, the capacity of the visual-spatial short-term memory can be measured [25].The participant will be seated in front of the examiner, who subsequently will tap the cubes starting with a sequence of two blocks. Two trials will be given per block sequence of the same length. If at least one of these is repeated correctly, the next two trials of a sequence of an increased length will be administered. The cubes will be touched with the index finger at a rate of approximately one cube per second (with no pauses between the individual cubes). The participant will have to tap the cube sequences in the same order immediately after the examiner finishes. The sequences will gradually increase in length. The test will be terminated if the participant fails to reproduce two sequences of equal length. Only a completely, correctly repeated sequence will be scored as correct; self-corrections will be permitted.Rapid visual information processing taskThe rapid visual information processing task (RVIP) is a serial detection task used to probe visual sustained attention and working memory processes. The design of the task consists of a stream of single digits (Arabic numerals 1–9) presented at a rate of 100–110 per minute. Participants are required to detect targets comprising a sequence of three consecutive odd or three consecutive even numbers. In a typical paradigm, targets are presented at a rate of four per 30 s. The critical performance variables include the number of correct responses (“hits”), the reaction time for hits, and the number of errors of commission (response in the absence of a target) [26].This RVIP version will be programmed using e-prime (Version 1.1. Psychology Software Tools, Inc., www.pstnet.com). White numbers between 0 and 9 (excluding 1) will appear in the center of a black computer screen. Each number is presented for 600 ms without a time gap between two succeeding numbers. The participant will have to detect three target sequences (“2–4–6”, “3–5–7”, and “4–6–8”) and respond to them (within 1800 ms after the onset of the last number) by pressing the space bar on the keyboard when the last number of a target sequence appears. The three target sequences will be displayed on the screen during the whole session in order to help the participants remember.Each block will be composed of 150 numbers that appear in a pseudo-random and fixed order; four target sequences will be included in 50 numbers. There will be 72 target sequences that appear during the 9-min test session. In order to prevent a sequence effect, six different RVIP versions will be created by varying these six blocks and then balancing them and pseudo-randomly assigning them to the participants. Hits (H), false alarms (FA) and reaction time (RT) will be recorded by the computer. All RTs shorter than or equal to 100 ms will be excluded from further analyses.

In a second step, the sensitivity A, measuring a subject's ability to distinguish targets and non-targets:$$ \left(\mathrm{A} = 0.5 + \left[\mathrm{P}\left(\mathrm{H}\right) - \Big(\mathrm{P}\left(\mathrm{FA}\right) + \left(\left(\mathrm{P}\left(\mathrm{H}\right) - \mathrm{P}\left(\mathrm{FA}\right)\right)2\right]/\right[4\mathrm{P}\left(\mathrm{H}\right)\left(1 - \mathrm{P}\left(\mathrm{FA}\right)\right)\right), $$

the response criterion B, reflecting the individual's response tendency:$$ \Big(\mathrm{B} = \left[\mathrm{P}\left(\mathrm{H}\right)\left(1 - \mathrm{P}\left(\mathrm{H}\right)\right) - \mathrm{P}\left(\mathrm{FA}\right)\left(1 - \mathrm{P}\left(\mathrm{FA}\right)\right)\right]/\Big[\mathrm{P}\left(\mathrm{H}\right)\left(1 - \mathrm{P}\left(\mathrm{H}\right)\right) + \mathrm{P}\left(\mathrm{FA}\right)\left(1 - \mathrm{P}\left(\mathrm{FA}\right)\right), $$

and the SD for the mean RT of each individual will be calculated. Sensitivity A, the number of hits, the SD and the mean RT will be evaluated from two perspectives: the level (e.g., the mean value of A over 9 min) and the time course (e.g., the mean value of A for the first 3 min, the second 3 min and the last 3 min). The number of FA and the response criterion B will be only evaluated from the perspective of level. The SD and the mean RT will only be computed for the hits [27].

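### The printed formula for RVIP sensitivity A is malformed and cannot be computed unambiguously; its most literal completion scores perfect detection the same as guessing

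*Protocol article*

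**What the plan says.** The RVIP description in the Methods (Secondary outcomes, cognitive tests, after Fig. 5) gives two formulas. The first defines a sensitivity index A, which is to reflect the participant's "ability to distinguish targets and non-targets". The second defines a response criterion B.

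Writing h for P(H) and f for P(FA), A is printed as

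`(A = 0.5 + [h - (f + ((h - f)2]/[4h(1 - f))`

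The raw data come from the task program: "Hits (H), false alarms (FA) and reaction time (RT) will be recorded by the computer". On use, the article says that "Sensitivity A, the number of hits, the SD and the mean RT will be evaluated from two perspectives", namely a level over the 9 minutes and a time course, for example "the mean value of A for the first 3 min, the second 3 min and the last 3 min". Statistical methods sends the RVIP scores to a paired comparison of the two interventions, with p < 0.05 as the threshold.

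The standing of the cognitive tests varies. The abstract lists RVIP among the secondary outcomes. The text below Fig. 4 says "as exploratory outcomes we will also assess cognitive functions" and, a few lines later, calls cognitive performance a secondary outcome.

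**The concern.** A discrimination index should be highest when every target is detected without false alarms, and should sit at a fixed floor when hits and false alarms are equally likely. The printed expression does not guarantee this. The round bracket opened after the minus sign is not closed before the plus sign, so it is unclear whether the minus governs only P(FA) or the following term as well. The 2 sits on the line, so it could be read as a power or as a factor.

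The sign of the last term decides whether A rises or falls with better detection. A programmer who closes the brackets at the end of the numerator would obtain a score on which a real gain in attention could appear as a loss, in a comparison meant to test whether the 4-step method improves cognitive performance.

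**Working it through.** **Inputs.** The formula and its stated purpose come from the RVIP text. The documents give no values of h or f. Those used here are assumptions: f from 0 to 0.2, and h from 1/72 (or f, if larger) up to 1.

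**The task's own figure.** Nine minutes at 600 ms per number is 540 / 0.6 = 900 numbers, or 6 blocks of 150. Four targets per 50 numbers gives 900 / 50 × 4 = 72, which agrees with "There will be 72 target sequences that appear during the 9-min test session". The task description is consistent; the difficulty lies only in the scoring formula. No value of A is stated, so there is none to reproduce.

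**Bracket count.** With P(H) and P(FA) written out, A has 11 opening and 9 closing round brackets, and 2 opening and 1 closing square brackets. B has 13 and 12 round, and 2 and 1 square. In B only the outer brackets are missing, so its meaning can be recovered. In A the unclosed round brackets are inside the numerator, where they affect the result.

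**Four completions.** Let D = 4h(1 − f).

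| Completion | Formula | h = 1, f = 0 | h = f |
|---|---|---|---|
| 1. Closed at the end of the numerator, 2 a square | 0.5 + [h − f − (h − f)²]/D | 0.5 + (1 − 1)/4 = 0.50 | 0.50 |
| 2. Closed at the end of the numerator, 2 a factor | 0.5 + [h − f − 2(h − f)]/D | 0.5 + (1 − 2)/4 = 0.25 | 0.50 |
| 3. Bracket dropped or closed after P(FA), 2 a square | 0.5 + [h − f + (h − f)²]/D | 0.5 + (1 + 1)/4 = 1.00 | 0.50 |
| 4. Bracket dropped or closed after P(FA), 2 a factor | 0.5 + [h − f + 2(h − f)]/D | 0.5 + (1 + 2)/4 = 1.25 | 0.50 |

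**Direction, completion 1.** At f = 0 it reduces to 0.5 + (1 − h)/4, which falls with every extra hit. For f > 0, the part that depends on h is −h − (f + f²)/h, which peaks at h = √(f + f²):
- f = 0.01: peak 0.707 near h = 0.10, then 0.626 at h = 0.5, 0.528 at h = 0.9 and 0.503 at h = 1.
- f = 0.1: peak 0.649 near h = 0.33, falling to 0.525 at h = 1.
- f = 0.2: peak 0.631 near h = 0.49, falling to 0.550 at h = 1.

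**Direction, completion 3.** The part that depends on h is h − (f − f²)/h. Its slope, 1 + (f − f²)/h², is positive for every f between 0 and 1, so A always rises with hits. At f = 0.01 it gives 0.869, 0.972 and 0.998 at h = 0.5, 0.9 and 1.

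**One participant improving on both rates.**

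| h, f | Completion 1 | Completion 3 |
|---|---|---|
| 0.80, 0.05 | 0.5 + (0.75 − 0.5625)/3.04 = 0.562 | 0.5 + (0.75 + 0.5625)/3.04 = 0.932 |
| 0.95, 0.01 | 0.5 + (0.94 − 0.8836)/3.762 = 0.515 | 0.5 + (0.94 + 0.8836)/3.762 = 0.985 |

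The same improvement lowers the score under one completion and raises it under the other.

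**The case against.** The strongest objection is that a reader might infer from the print that the trial's scoring rule subtracts the squared term. The text does not establish that. With the bracket never closed, the sign of that term is undetermined, and completion 3 is well behaved. The unmarked exponent and the missing brackets in B point to a fault of notation, typesetting or conversion affecting both equations, rather than to a chosen scoring rule. An unbalanced expression also cannot be programmed as it stands: someone must repair it first, and the purpose stated in the same sentence steers that person towards the sensible repair.

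All of this stands, and it limits the point to ambiguity. It does not remove it. The extra opening bracket is present in the text and is not merely a lost character, and superscripts survive elsewhere in the article. The literal repair, closing what is open at the end of the numerator, is the one that fails.

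A reader might also infer that the cognitive conclusion of the trial could be reversed. That goes too far. RVIP is one of four cognitive tests, and A is one of several RVIP measures. The task description names hits, reaction time for hits and errors of commission as the critical variables. These do not depend on the formula, and a mis-scored A would visibly disagree with them.

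**Conclusion.** The point holds as a defect of specification. As printed, A has no single value: perfect detection scores 0.50, 0.25, 1.00 or 1.25 according to how the expression is completed. Under the most literal completion with a square, perfect detection equals guessing at 0.50 and A falls with more hits over most of the range examined, which contradicts its stated purpose. The numerical illustrations rest on assumed hit and false-alarm rates; the values at perfect detection and at equal rates do not.

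The consequence is limited to one derived score, analysed as level and time course, in one cognitive test whose status is given as both secondary and exploratory. The primary hypoglycemia outcome and the sample size are not affected. The documents do not show that a wrong formula will be used. If the full protocol or the scoring program already carries balanced brackets and an explicit square with the term added, only the article's wording needs correction.

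**What to change.** Restate the formula as

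`A = 0.5 + [(P(H) - P(FA)) + (P(H) - P(FA))^2] / [4 P(H) (1 - P(FA))]`

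Of the four completions, this is the only one that gives both 1.0 for perfect detection and 0.5 when P(H) = P(FA), so it can be justified from the stated purpose alone. Add the missing outer brackets to B. Before any data are scored, run the scoring code on those two anchor cases and record the result. The cost is one corrected line, a bracket repair in B and two test cases; no design element or data collection changes.
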